## Abstract

**Background:**

Chronic low back pain remains a major health problem in Australia and around the world. Unfortunately the majority of treatments for this condition produce small effects because not all patients respond to each treatment. It appears that only 25–50% of patients respond to exercise. The two most popular types of exercise for low back pain are graded activity and motor control exercises. At present however, there are no guidelines to help clinicians select the best treatment for a patient. As a result, time and money are wasted on treatments which ultimately fail to help the patient.

**Methods:**

This paper describes the protocol of a randomised clinical trial comparing the effects of motor control exercises with a graded activity program in the treatment of chronic non specific low back pain. Further analysis will identify clinical features that may predict a patient's response to each treatment. One hundred and seventy two participants will be randomly allocated to receive either a program of motor control exercises or graded activity. Measures of outcome will be obtained at 2, 6 and 12 months after randomisation. The primary outcomes are: pain (average pain intensity over the last week) and function (patient-specific functional scale) at 2 and 6 months. Potential treatment effect modifiers will be measured at baseline.

**Discussion:**

This trial will not only evaluate which exercise approach is more effective in general for patients will chronic low back pain, but will also determine which exercise approach is best for an individual patient.

**Trial registration number:**

ACTRN12607000432415

## Background

### The problem of chronic low back pain

Low back pain is extremely costly causing great economic burden for Australia's health system, and considerable suffering for the individual [1]. Around 60–80% of the population will at some time exhibit low back pain [2-5] and of these 70 to 80% will have at least one recurrence [6]. Despite the enormous amount of resources directed to the treatment of chronic low back pain world wide, treatment for this health condition continues to have a low success rate [7-9]. The search for more effective ways to manage chronic low back pain is critical if we are to improve the health and quality of life for many Australians.

### Which exercise approach for chronic low back pain?

In Australia the most frequently used treatment for chronic low back pain is exercise [9]. Exercise, however, is not a single treatment. The types of exercise programs for chronic low back pain vary widely e.g. land-based exercise versus exercise in water, individual exercise versus group exercise, isolated trunk exercise versus whole body exercise. Unfortunately there is little or no evidence to help clinicians select the most effective type of exercise for an individual patient. This absence of evidence means that care is likely to be sub-optimal.

While some trials of exercise have reported large, durable and clinically important effects [10] others have not [11] Because the types of exercise programs for chronic low back pain vary widely [7] and patient presentations also vary widely it is unlikely that all programs are equally effective for all patients. Further, close examination of results of trials reveals that even in the positive trials not all the subjects had a good outcome. Consequently, a single summary statement on the effectiveness of 'exercise' for chronic low back pain would not be meaningful. This would be analogous to attempting a summary statement on the efficacy of 'drugs' for chronic low back pain, an approach that ignores the different classes and doses of drugs used in the treatment of low back pain.

Two very different approaches to exercise are motor control exercise [12] (sometimes called specific spinal stabilisation exercise) and a graded activity program [13] At present it is unclear which form of exercise is more effective in the management of chronic low back pain. In a literature review McGuirk [14] concluded that the motor control approach is the only exercise therapy that has been shown to achieve substantial and lasting reductions in pain. In contrast the 2004 European guideline [15] for management of chronic non-specific low back pain concludes: 'the use of a cognitive-behavioural approach, in which graded exercises are performed, using exercise quotas, appears to be advisable' (p 85). Despite this controversy, in New South Wales (NSW) WorkCover in Australia has decided that graded activity is the preferred approach and has commenced training each physiotherapist, chiropractor and osteopath (~2,300 practitioners) to implement this treatment. Within the physiotherapy profession this course of action has been questioned as not all believe that graded exercise is the preferred approach for all patients. There has been a considerable debate regarding the most appropriate form of supervised exercise for chronic low back pain, however, at present there is no evidence to inform this debate because there has never been a direct comparison of the two approaches.

Informed prescription of exercise requires evidence on the effectiveness of each type of exercise; and decision algorithms to assist clinicians to select the best form of exercise for an individual patient. This information is not currently available and clinical practice is likely to be suboptimal. The ability to identify patients with a greater chance of success has the potential to establish new knowledge, and save time and money associated with unsuccessful treatment. This is a unique goal of the proposed study.

### Predicting response to treatment

Most people with chronic low back pain are considered to have 'non-specific' low back pain, that is, they have no definitive structural diagnosis. It is a widespread clinical belief that it is possible to use clinical features to identify sub-populations of patients with non-specific low back pain who respond differently to treatment and there is some early evidence to support this view [16-18]. Recently Childs and colleagues [17] found that manipulative treatment resulted in a 50% reduction in pain for 44% of patients in their study. However a patient who was positive on their prediction rule had a 91% probability of a successful outcome with manipulation, while a patient who was negative had only a 7% probability of responding. At present there is no similar rule for exercise treatment of chronic low back pain. This is a major gap in knowledge. Not only will our proposed study determine which exercise approach is more effective in general for patients with chronic low back pain, but it will also determine which exercise approach is best for an individual patient. The identification of clinical features that predict response to treatment will save the enormous amounts of time and money that are currently wasted on unsuccessful exercise programs. With the large prevalence of chronic low back pain even modest predictive ability could make a substantial contribution to health systems worldwide.

## Methods and Discussion

### Overview of research design

The study will be a randomised controlled trial comparing graded activity and motor control exercise for patients with chronic low back pain. Each exercise program will consist of 12 individually supervised hour sessions over an eight-week period, 2 additional follow-up treatments at 4 and 10 months and a home exercise program. Outcomes will be measured at 2 months, 6 months and 12 months from baseline. Putative predictor variables will be taken from the baseline clinical assessments. The study design, procedures and informed consent were approved by The University of Sydney Human Research Ethics Committee.

### Hypothesis

i) That motor control exercise will be more effective in improving pain and disability at 2, 6 and 12 months.

ii) The effect of graded activity (versus motor control) is greater in patients who are deconditioned and have negative beliefs about their pain.

iii) The effect of motor control exercise (versus graded activity) is greater in patients with impaired control of movement and stability of the spine.

### Subject recruitment

A total of 172 subjects will be recruited from general practitioners, physiotherapy practices and public hospitals in Sydney and Brisbane. Contact has been made with these sites and consent letters have been obtained. Subjects will be screened to identify those who are unsuitable for exercise management of their low back pain because of significant co-morbidity such as serious spinal pathology or contraindication to exercise. To screen for serious pathology, the physiotherapist will conduct a diagnostic triage following the Royal College of General Practitioners' low back pain guidelines [19] and will be screened for contraindications to exercise as listed in the ACSM guidelines [20].

Subjects will be included if they meet all of the following **inclusion **criteria:

• Non-specific low back pain +/- leg pain persisting for at least 3 months duration

• Currently seeking care for low back pain

• Aged more than 18, less than 80 years

• English speaker

• Clinical assessment indicates that the subject is suitable for active exercises

• Expects to continue residing in the Sydney or Brisbane region for study duration

• Obtains a score of moderate or greater on question 7 or 8 of the SF-36.

(*Question 7 *– How much bodily pain have you had during the past week? None, very mild, mild, moderate, severe, very severe).

(*Question 8 *– During the past week, how much did pain interfere with your normal work, including both work outside the home and housework? Not at all, a little bit, moderately, quite a bit, extremely) [21].

Subjects will be **excluded **if they have any of the following:

• Known or suspected serious spinal pathology (fracture, metastatic, inflammatory or infective diseases of the spine, cauda equina syndrome/widespread neurological disorder).

• Nerve root compromise (at least 2 of the following signs: weakness/reflex changes/sensation loss, associated with the same spinal nerve)

• Previous spinal surgery or scheduled for major surgery during the treatment follow-up period

• Co-morbid health conditions that would prevent active participation in the exercise programs.

Specific spinal pathology or contraindication to treatment may be suspected based upon the results of the screening questionnaire and the Physical Activity Readiness Questionnaire. If the assessor suspects the presence of any pathology or contraindication to treatment, these subjects should be further investigated by a registered physiotherapist and medical clearance obtained if necessary.

Subjects receiving workers compensation will only be included in the trial if they have written consent from the nominated treating doctor, insurer and employer agreeing to their participation in the trial. The letters should state that they agree with the condition that only the trial treatments will be administered to the patient and acknowledges that the patient will be instructed not to seek other treatments during the trial treatment period.

### Assessment and Allocation

#### Randomisation

Participants will be allocated to treatment group using sealed opaque envelopes. Physiotherapists will allocate patients by drawing the next consecutive envelope allocated to their practice. A sticker containing the letter M (motor control) or G (graded activity) will be inside the envelope. After reading the sticker it will be attached to the patient's file. The therapist will not reveal the patient's allocation until the end of the study.

#### Outcome measures

Following the screening consultation, personal characteristics (age, gender, ethnicity, religion, weight, height. level of education, employment status, doctor's details and contact information) and information about symptoms of low back pain will be collected. The following treatment outcomes will be measured at baseline, 2 months, 6 months and 12 months.

##### Primary Outcome (at 2 and 6 months)

1. Average pain intensity over the last week (0–10 scale) [22,23]

2. Patient-generated measure of disability (Patient-Specific Functional Scale) [22,23]

##### Secondary Outcomes

3. Patient's global impression of change (Global Change) [22,23]

4. Condition-specific measure of disability (Roland Morris Disability Questionnaire) [24]

5. Generic measure of health status (SF-36 Version I) [21]

In addition subjects will be asked about their pain (average for preceding 24 hours and their average pain in the preceding week) once a month during one year. This data will be collected using a SMS (phone message) system. A SMS message will be sent monthly to all subjects reminding them to text the researcher with a number from 0–10 representing their average pain intensity over the preceding 24 hours and a number representing their average pain intensity over the preceding week. If subjects do not have a mobile phone they will be e-mailed monthly and asked to supply their average pain intensity score via return email. For patients that do not have a mobile phone or access to email, the average pain intensity will be recorded by phone. At the end of the study all participants will receive $10.00 to cover the cost of text messaging. A summary measure of the pain experienced over the 12-month period is provided by the area under the curve of the pain intensity/time curve. These measurements may better reflect the fluctuating nature of chronic pain than is possible with traditional outcome measures taken at a single time point. As the measures are novel the measurement properties are unclear and so we will regard this as a secondary outcome.

To maximise attendance at follow-ups subjects will receive a reminder letter and a phone call 24 hrs prior to their appointment. Every attempt (within ethical constraints) will be made to obtain outcome data, regardless of subject's compliance with trial protocols. Follow-up measures will be scored by an investigator who is blinded to group allocation. At 2 months, information about side effects of treatment will be collected from all subjects using open-ended questioning. At each follow-up, information on use of other pain-related treatments will be recorded as will the patient's compliance with their home exercise program.

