### Interventions

Subjects in each group will receive 12 one-hour treatments over an 8 week period, i.e. 2 sessions/week in the first month and 1 session/week in the second month and 2 additional 1 hour follow-up sessions at 4 & 10 months. Patients will be advised to do home exercises for at least half an hour per week in the first month and one hour per week in the second month. However, the type of exercises, intensity and amount done per day will be performed at the discretion of the physiotherapists. The treatment session and home exercises will add up to 20 hours of treatment. In both exercise programs an individualised program for each patient is prescribed. The treatment sessions are designed to become less frequent over time to encourage independence. Patients with continued pain following all sessions will be asked to continue their home exercise program until pain-free for a week. If a recurrence occurs, re-initiation of the home program will be advised. This is consistent with current clinical practice.

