Generalised (whole body) exercises with consideration of specific muscle activity	X	√
Generalised (whole body) exercises without consideration of specific muscle activity	√	X
Specific (localised) exercises	X	√
Focus on correct activation of muscles	X	√
Correction of posture	X	√
Strength training	√	√
Cardiovascular/Fitness training	√	√
Coordination training	X	√
Correction of motor patterns	X	√
Muscle stretching	√	√
Breathing pattern	X	√
Consideration of continence	X	√
Correction of provocative movement patterns	X	√
Relaxation techniques	X	√
Progression to functional activities	√	√
Use feedback (e.g. US, EMG, biofeedback) to enhance learning of movement pattern or muscle activation.	X	√
Home exercises	√	√

Subjects in each treatment group will be asked not to seek other treatments for their chronic low back pain and where possible not to change current medications during the treatment period. Several mechanisms will be used to ensure that the trial protocol is consistently applied. Protocol manuals have been developed and staff will be trained to ensure that screening, assessment, randomisation and treatment procedures are conducted according to protocol. To ensure standardisation we will hold regular meetings with site visits. An independent researcher will monitor a randomly chosen subset to ensure adherence to assessment, randomisation and treatment procedures. Medical practitioners will be asked not to request the subject's allocation unless it is deemed necessary for medical care. At the completion of the exercise program, patients will be encouraged to continue the home exercise routine demonstrated at the discharge session. Subjects will be free to seek other treatment after the experimental period.

At 2 moths follow-up information about side-effects of treatment will be collected using open-ended questioning. Also at 2 months the compliance with the home exercises during the 8 weeks of treatment will be assessed. At 6 and 12 months open-ended questions about recurrence, recovery and about other treatment received for their low back pain during the study period will be sought. Reported recurrence can be compared against that recorded from the monthly SMS data.

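### No question about side effects is planned after the 2-month follow-up, although supervised sessions and home exercise continue beyond it

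*Protocol article*

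**What the plan says.** **Side effects.** The protocol article gives the timing twice. Under Secondary Outcomes: "At 2 months, information about side effects of treatment will be collected from all subjects using open-ended questioning". Under Interventions, after Table 1: "At 2 moths follow-up information about side-effects of treatment will be collected using open-ended questioning". Neither place names a later time.

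**Later follow-ups.** The Overview of research design states: "Outcomes will be measured at 2 months, 6 months and 12 months from baseline". For the last two of these, Interventions lists the topics: "At 6 and 12 months open-ended questions about recurrence, recovery and about other treatment received". Side effects are not among them.

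**Treatment.** Interventions describes the main block, "Subjects in each group will receive 12 one-hour treatments over an 8 week period", and adds "2 additional 1 hour follow-up sessions at 4 & 10 months". On home exercise it says: "Patients with continued pain following all sessions will be asked to continue their home exercise program until pain-free for a week". It also advises restarting the home exercises after a recurrence, and encourages all patients to keep them up once the supervised block is over.

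**Compliance and other treatment.** Secondary Outcomes has both recorded at every follow-up. Interventions says "at 2 months the compliance with the home exercises during the 8 weeks of treatment will be assessed" and mentions other treatment in its list for 6 and 12 months.

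**The concern.** The period over which side effects are asked about is shorter than the period over which trial treatment is given. Both arms have supervised sessions after 2 months, and both are directed towards continuing home exercise. If a patient is harmed by a later session or by long-running home exercise, no planned question would bring it out as a side effect.

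The trial is meant to guide the choice between two exercise programs and follows benefit for 12 months. Any account of side effects by arm would rest on the first 2 months alone, and what is not asked at follow-up is hard to recover afterwards.

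A lesser matter is that the two descriptions of process data are worded differently. Staff who built the follow-up forms from Interventions alone could leave out compliance at 6 and 12 months and other treatment at 2 months.

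**Working it through.** No sample size, power or error rate enters this point. The check is a comparison of the schedules plus simple arithmetic on treatment exposure.

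**Step 1: reproduce the article's treatment total.** Inputs, all from Interventions: two sessions a week in the first month, one a week in the second, one hour each; two further one-hour sessions; home exercise of at least 0.5 hours a week in the first month and 1 hour a week in the second. The 8 weeks are taken as two months of 4 weeks.

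- Sessions in the main block: 2 × 4 + 1 × 4 = 12, as stated.
- All supervised sessions: 12 + 2 = 14.
- Hours: 12 + 2 + (0.5 × 4) + (1 × 4) = 20, as stated.

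The stated total therefore includes the two later sessions. The article itself counts them as trial treatment.

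**Step 2: split the exposure at the 2-month enquiry.**

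| Quantity | By 2 months | After 2 months | Share after |
|---|---|---|---|
| Supervised sessions | 12 | 2 | 2/14 = 14% |
| Counted treatment hours | 12 + 6 = 18 | 2 | 2/20 = 10% |
| Home exercise after week 8 | none | not counted | cannot be computed |

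The last row is open because the article gives neither an amount nor an end date for later home exercise. Any such exercise raises the share falling after 2 months.

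**Step 3: set planned questions against follow-ups.**

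| Item | Secondary Outcomes | Interventions |
|---|---|---|
| Side effects | 2 months | 2 months |
| Compliance at home | 2, 6, 12 months | 2 months, for the 8 treatment weeks |
| Other treatment | 2, 6, 12 months | 6 and 12 months, looking back over the study |
| Recurrence, recovery | not mentioned | 6 and 12 months |

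On side effects the two sections agree, and neither goes past 2 months. On compliance and other treatment they differ in wording, but both can be followed at once: Secondary Outcomes gives the general rule, and nothing in Interventions limits it.

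**Step 4: see what else might pick up later side effects.** Monthly pain scores run for a year. Pain, function, disability, health status and global change are measured at 6 and 12 months. Worsening back pain could show in these. None of them asks whether treatment caused a problem, and a problem away from the back might not register.

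**The case against.** **Timing and exposure.** The enquiry comes at the end of the intensive block, where 18 of the 20 counted hours (90%) and 12 of the 14 sessions (86%) fall. What follows is a light maintenance phase. Home exercise then depends on continued pain or recurrence, or is only encouraged. Patients may also use other care once the experimental period ends, so later complaints are harder to attribute. All of this stands. It limits the size of the gap but does not close it.

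**Condensed article.** An article leaves much to the full protocol, and spontaneous reporting of adverse events may be described there. That cannot be excluded, so the point is that no enquiry after 2 months is planned here, not that later side effects can never come to light. Even so, this is more than an omission: the article fixes the time point twice and itemises the later questions without side effects.

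**Stronger readings that a reader might infer.**

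- *Five-sixths of exposure goes unobserved.* The 2-month enquiry does leave 10 of 12 months (83%) uncovered, but that is follow-up time. Counted treatment is concentrated in the first 8 weeks.
- *The two sections contradict each other on compliance and other treatment.* Interventions does not say that its times are the only ones. This is loose wording.
- *Other treatment during the first 8 weeks goes unrecorded.* Secondary Outcomes records it at every follow-up, including 2 months, and the later question in Interventions reaches back over those weeks by recall. The documents do not support this reading.
- *A planned harms analysis is undermined.* The Data analysis section describes none, and such an analysis may properly be left to an analysis plan that is not shown.

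**Conclusion.** The point holds in a limited form. The article schedules side-effect questioning at 2 months and at no later time, while its own treatment programs continue. The uncovered part is 2 of 14 supervised sessions and 2 of 20 counted hours, plus home exercise of unstated amount. Other planned measures would reveal some later side effects indirectly and would miss others.

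This rests on two assumptions: that the article's schedule is what sites follow, and that no fuller document adds a later enquiry. The primary outcomes, sample size and error rate are untouched. The change is worth making because it is cheap and late collection is unreliable. The difference in wording on compliance and other treatment is a minor drafting matter.

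**What to change.** 1. At the existing 6- and 12-month follow-ups, ask the same open-ended side-effect question as at 2 months, and record the date of onset. Each question would then come 2 months after a later session (6 − 4 = 2 and 12 − 10 = 2), and the onset date would separate early from late events.
2. Report side effects by arm over 12 months, showing those with onset after 2 months separately because their attribution is weaker.
3. Bring Interventions into line with Secondary Outcomes, so that both say that compliance at home and other treatment are recorded at 2, 6 and 12 months.

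The cost is one question at each of two follow-ups that already take place, with a little more data entry. The drawback is that late events are harder to ascribe to trial exercise once patients may use other care; the record of other treatment helps in reading them. The third change affects wording only. None of the three alters treatment.

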• The *graded activity *program is based upon the treatment approach reported by Lindstrom [40] and identical to the protocol we used in a previous trial [13]. At the first visit the physical demands of subjects' work and home activities will be established and measures of mobility, strength and aerobic fitness taken. From these assessments an individualised, submaximal, progressively incremented exercise program will be developed to train those functions found to be inadequate for performance of work or leisure activities. The goal is to improve the subject's ability to complete functional activities they specify as being difficult to perform because of the low back pain. Principles underlying cognitive-behavioural therapy will be used by the physiotherapists in their training and supervision role. These principles include the encouragement of skill acquisition by modeling the exercises, providing information, setting progressively raised goals, self-monitoring of progress, and verbally reinforcing progress made by subjects towards their goals. Fear of increased pain or even possible (re)injury will be addressed by discussion of the realistic chances of exercises causing injury, by ensuring that subjects set initial goals well within their capabilities (to maximise the chances of early success experiences), and by encouraging subjects to maintain a graded increase in exercises and other activities with regular rest breaks and frequent reflection on achievements.

Each subject will carry out a form of aerobic exercise (e.g. walking or cycling), stretches, functional activities, activities to build speed, endurance and coordination and trunk and limb strengthening exercises. Subjects will be given an individualised home exercise program that will be regularly evaluated by the physiotherapist.

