• The *motor control *exercise program is based upon the treatment approach reported by Richardson et al [27], O'Sullivan et al [10] and Moseley [41] and similar to the protocol we used in an earlier trial [12]. The approach utilises the principles of motor learning to retrain the optimal control and coordination of the lumbar spine and pelvis. Stage one involves regaining basic control strategies. This often involves training the pre-activation of the deeper muscles of the trunk such as transversus abdominis, multifidus, pelvic floor and diaphragm muscles that are typically affected in the presence of pain. The strategies that are selected are based on the patients presenting changes in coordination. Therapists will also assess and train posture and movement dysfunction (e.g. provocative movements and poor control strategies). Basic principles of motor learning such as simplification, segmentation, augmented feedback and practice are used to retrain the ideal activation of the deep muscles. Recent data suggests that these strategies restore control of the deep muscles [42] and lead to persistence of the change after cessation of treatment [43,44]. In this stage of training therapists will have access to a range of strategies that are typical in clinical practice including ultrasound imaging for feedback of muscle contraction, EMG biofeedback and other tools [27]. Other targets of this stage include coordination of breathing and changes at adjacent segments (e.g. hip, thoracic spine). In stage 2 participants will be progressed though to more complex static and dynamic tasks, and training of functional activities. At all progressions the therapist evaluates and corrects trunk muscle recruitment strategies, posture, movement patterns and breathing. Session 12 is a discharge session where the patient's progress will be reviewed and patients will be prescribed exercises to continue at home.

A treatment demarcation table was developed to help the trial clinicians to identify salient features from each of the interventions and to avoid unintended contamination between the two treatment approaches (see Table 1).

**Table 1 T1:** Treatment Demarcation

**Principles**	**Graded Activity**	**Motor Control**
Goal setting	√	√
Pain contingent	X	√
Time contingent	√	X
Quotas/Pacing	√	X
Reinforce well behaviour and ignore illness behaviour	√	X
Education regarding pain system and reassurance	√	√
Education regarding ergonomic factors and body awareness	√	√

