### Justification of study design

#### Controlling bias

The trial includes key methodological features that have been recognised as minimising bias in clinical trials: true randomisation, concealed allocation, specification of eligibility criteria, blind outcome assessment, patient blinding, blind analysis and intention-to-treat analysis. The nature of the treatments precludes blinding of patient and treatment provider.

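### The one side-effect question described relies on unblinded patients' attribution, and the arms handle pain and illness behaviour differently, so by-arm side-effect counts are open to differential reporting of unknown size

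*Protocol article*

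**What the plan says.** Secondary Outcomes states: "At 2 months, information about side effects of treatment will be collected from all subjects using open-ended questioning". Interventions repeats it for the 2-month visit: "follow-up information about side-effects of treatment will be collected using open-ended questioning". For the later visits the topics are given as: "At 6 and 12 months open-ended questions about recurrence, recovery and about other treatment received for their low back pain during the study period will" (end of sentence omitted). Side effects are not named there. No other harms measure is described, and Data analysis mentions no comparison of side effects between arms.

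Controlling bias lists patient blinding among the trial's features but then says "The nature of the treatments precludes blinding of patient and treatment provider". I take the second statement as governing. Follow-up measures are scored by an investigator blind to allocation (Secondary Outcomes).

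Table 1 in Interventions separates the programs. "Reinforce well behaviour and ignore illness behaviour" is ticked for graded activity and crossed for motor control. "Pain contingent" is crossed for graded activity and ticked for motor control. "Education regarding pain system and reassurance" is ticked for both. The graded activity text adds: "Fear of increased pain or even possible (re)injury will be addressed by discussion of the realistic chances of exercises causing injury". The motor control text has no equivalent.

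**The concern.** The described enquiry is open-ended and concerns effects of the treatment. A patient who has a flare but does not blame the exercise has, on the natural reading, nothing to report. Blind scoring does not protect such an item, because the judgement is made by a patient who knows which program was received.

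This goes beyond a general complaint about open-ended questions. One program directs therapists away from responding to illness behaviour, does not let pain govern the exercise, and discusses how likely exercise is to cause injury. The other uses pain to guide exercise. The interventions may therefore act on the same attribution that the measure depends on. The same flare could be called a side effect in one arm and an expected part of the program in the other.

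At stake is the description of harms that readers will set beside the efficacy results. The trial aims to say which program suits which patient, and side-effect counts by arm will enter that choice even without a formal test. The counts could show a difference that is not real, or mask one that is.

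**Working it through.** The documents give no harm rate, no reporting rate and no power statement for harms, so there is no figure of the plan's own to reproduce. The check has two parts.

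**1. The passages side by side**

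| Feature | Graded activity | Motor control | Source |
|---|---|---|---|
| Illness-behaviour row | yes | no | Table 1 |
| Pain-contingent row | no | yes | Table 1 |
| Counselling on fear of re-injury | described | not described | Interventions, program texts |
| Education and reassurance about pain | yes | yes | Table 1 |
| Patient blinded | no | no | Controlling bias |
| Open-ended question at 2 months | yes | yes | Secondary Outcomes; Interventions |

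The first three rows differ between arms and bear on whether a patient would call a flare a side effect. The fourth does not separate the arms. The question itself is the same in both.

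**2. Illustration of size (assumptions, not document figures)**

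Inputs from the Sample size calculation: 86 per arm and up to 10% loss, so 86 × 0.9 = 77.4, about 77 followed per arm. Assumed: the same true risk p in both arms, and a share s of events reported that differs by arm.

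Apparent risk = p × s. Apparent risk ratio (graded activity / motor control) = s(graded activity) / s(motor control), whatever the value of p.

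The chance of a two-sided 5% result in the direction shown is Φ[(|Δ| − 1.96 × SE₀) / SE₁]. Here SE₀ = √(2p̄(1 − p̄)/77), where p̄ is the mean of the two apparent risks, and SE₁ = √([p₁(1 − p₁) + p₂(1 − p₂)]/77).

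Worked case with p = 0.20, 80% reported under motor control and 40% under graded activity:
- apparent risks 0.20 × 0.80 = 0.16 and 0.20 × 0.40 = 0.08; ratio 0.50; Δ = 0.08
- SE₀ = √(2 × 0.12 × 0.88/77) = 0.0524
- SE₁ = √((0.1344 + 0.0736)/77) = 0.0520
- (0.08 − 1.96 × 0.0524)/0.0520 = −0.44, so the chance is 33%

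| True risk, both arms | Reported: motor control / graded activity | Apparent risk: motor control v graded activity | Ratio | Chance of a spurious result |
|---|---|---|---|---|
| 10% | 80% / 60% | 8% v 6% | 0.75 | 7% |
| 10% | 80% / 40% | 8% v 4% | 0.50 | 18% |
| 20% | 80% / 80% | 16% v 16% | 1.00 | 5% (nominal) |
| 20% | 80% / 60% | 16% v 12% | 0.75 | 11% |
| 20% | 80% / 40% | 16% v 8% | 0.50 | 33% |
| 20% | 60% / 80% | 12% v 16% | 1.33 | 11% |
| 30% | 80% / 60% | 24% v 18% | 0.75 | 15% |
| 30% | 80% / 40% | 24% v 12% | 0.50 | 49% |

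If motor control reported 90%, the ratios would be 60/90 = 0.67 and 40/90 = 0.44. The ratio only restates the assumed reporting rates. The table shows that modest differences in reporting could matter, not that they will occur. The last column applies only if someone tests the difference, which the article does not plan.

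**The case against.** The case on the other side is substantial, and much of it stands.

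- **Direction.** A reader might infer that the harms comparison is biased so as to make graded activity look safer. The documents do not show this. The illness-behaviour row is a principle for trial clinicians. It does not tell patients to withhold anything from the follow-up assessor. Discussing injury risk could make patients more alert to harm as well as less. True flare rates may also differ, because only one program is pain contingent. This question could not separate such a real difference from a reporting one.
- **Reassurance.** A reader might infer that only one arm is reassured about pain. Table 1 ticks that row for both.
- **Counting rule.** A reader might infer that an event counts only if the patient blames the exercise. The article gives neither the question's wording nor a counting rule, and it says protocol manuals exist. What it does fix is the object of the enquiry, its open form and its timing, and that object is attributional. The point rests on that and on nothing omitted.
- **Other data.** Worsening pain is partly captured without attribution, through the scores at each follow-up, the Global Change rating and the monthly 0–10 reports. This narrows the point. However, the article plans to use the monthly scores as an area under the curve and as a check on reported recurrence, not as harms, and an average area can hide patients who got worse.
- **No test planned.** This is correct, so no planned analysis is invalid. Side effects will nevertheless be collected in both arms, and counts by arm will be read comparatively.
- **Limits of the remedy.** Any replacement is still unblinded self-report. That is accepted.

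**Conclusion.** The concern holds in a limited form. The only side-effect measure described is one open-ended enquiry at 2 months about effects of treatment, put to patients who know their program. The arms differ in three respects that bear on attribution. Any by-arm description of side effects is therefore open to differential attribution and reporting. Favouring graded activity is the plausible direction, but it is not demonstrated.

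The size cannot be obtained from the documents. With equal true risk, reporting of 80% against 60% or 40% gives an apparent ratio of 0.75 or 0.50. Equal reporting gives 1.00, and the reverse pattern (60% against 80%) gives 1.33. All of these depend on assumed reporting rates.

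The efficacy outcomes, the sample size and the interaction analyses are not affected. This is an inexpensive improvement to harms measurement and does not correct an invalid analysis.

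**What to change.** 1. Keep the open-ended question. Before it, have the blinded assessor ask both arms one identical attribution-free item, for example: since starting the program, have you had any new or worse pain, or any other new health problem, lasting more than a day?
2. Report all such events by arm, whatever their perceived cause. Give the volunteered side effects as supporting information.
3. From data already collected, tabulate by arm the number of patients whose Global Change rating is worse and the number whose 0–10 pain score has risen from baseline by an amount fixed in advance (2 points is one option).
4. State with the results that all of these are unblinded self-reports.

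The cost is one added question on the 2-month form and one extra table. Raw counts will rise in both arms and will include events unrelated to exercise. The change takes causal attribution out of the count. It does not remove every difference in how patients in the two arms perceive or report pain.
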